## Abstract

**Background:**

With an increasing number of people with dementia worldwide and limited advancement in medical treatments, the call for new and cost-effective approaches is crucial. The utility of self-management has been proven in certain chronic conditions. However, very little work has been undertaken regarding self-management in people with dementia.

**Methods:**

The SHAPE trial will include 372 people with mild to moderate dementia to evaluate the effectiveness and cost-effectiveness of an educational programme combining approaches of self-management, health promotion, and e-learning for care partners. The study is a multi-site, single-randomised, controlled, single-blinded trial with parallel arms. The intervention arm is compared with treatment as usual. The intervention comprises a 10-week course delivered as group sessions for the participants with dementia. The sessions are designed to develop self-management skills and to provide information on the nature of the condition and the development of healthy behaviours in a supportive learning environment. An e-learning course will be provided for care partners which covers similar and complementary material to that discussed in the group sessions for the participant with dementia.

**Discussion:**

This trial will explore the effect of the SHAPE group intervention on people with mild to moderate dementia in terms of self-efficacy and improvement in key health and mental health outcomes and cost-effectiveness, along with carer stress and knowledge of dementia.

**Trial registration:**

ClinicalTrials.gov Identifier: NCT04286139, registered prospectively February 26, 2020, https://clinicaltrials.gov/ct2/show/NCT04286139

## Background

The recent Lancet Commission report on dementia estimated that 47 million people were living with dementia in 2017 [1]. As the world’s population grows older, this number is expected to double every 20 years [2]. With limited advancement in medical treatments combined with increasing pressures on limited resources, novel and cost-effective approaches are needed to reduce the impact of the disease at the individual and societal levels. More effective self-management is central to achieving this objective and has the potential to avoid unnecessary excess disability or premature loss of function and institutionalisation [3, 4]. There is a growing body of evidence for the health and economic benefits of other interventions for people with dementia [5] and for their care partners [6], but so far, little has been done to increase knowledge on the clinical and economic case for self-management, health promotion and e-learning. A number of countries have developed national strategies for dementia and emphasised the importance of providing disease-related information for the person affected by the disease and not just for the care partner [7, 8]. Health plans, in countries including Norway [9] and United Kingdom (UK) [10], are responding to the health needs of individuals with dementia and their families, as well as identifying better ways to care for people with dementia. These policies [11] aim to help citizens stay in their homes for longer, based in part on an economic motivation to address the total direct and formal care cost of dementia, particularly because admission to 24-h care is expensive [12]. Despite the importance of self-management, very little work has been undertaken on either health promotion or self-management in people with dementia.

A recent systematic review [13] focused on self-management for people with dementia and mild cognitive impairment (MCI), and outlined the key components of self-management interventions. It found that while some interventions included some key components of self-management, only two studies specifically reported self-management programmes, and neither of these presented quantitative outcomes. The SMART trial, a pilot randomised controlled trial (RCT) [14] showed quantitative positive findings regarding self-efficacy, and showed high satisfaction as reported qualitatively. Another RCT of self-management [15] also demonstrated beneficial effects on the health-related quality of life of spouses and the cognitive function of persons with dementia. Benefits of self-management include improved knowledge, task performance, self-efficacy and aspects of health status [16, 17]. Most empirical work has focused on the self-efficacy component of this model. Self-efficacy is defined as belief in one’s ability to succeed or to accomplish a specific action in a particular situation [18]. The utility of self-management is long proven for outcomes of other chronic diseases [19, 20]. We have found that people with early-stage dementia are usually able to identify areas of their lives, such as exercise, social activities and recreational pursuits, which they would like to manage better [21, 22], which in turn could improve quality of life and well-being. This offers an avenue for a sensitive and tailored approach to encourage individuals receiving a diagnosis of dementia to draw on their resources and on support from others to make positive changes. Health promotion includes self-management components such as developing personal skills; but also covers a wider set of approaches such as public policy, supportive environments, community actions and health service perspectives [23].

Evidence exists for the need to assist persons with early-stage dementia with health promotion to sustain their function, quality of life, well-being, and prevent premature loss of function or institutionalisation [24]. Buettner and Fitzsimmons [4] demonstrated significant positive change in cognition and depression in their health promotion intervention. The intervention has been adapted and applied to a Norwegian context [25], where a quasi-experimental study including 108 persons with early-stage dementia was conducted. Findings from this study showed a significant improvement in depressive symptoms and self-rated health in early stage dementia, and participants’ MMSE scores stayed stable during the 4-month follow-up, which was statistically significantly different from the average decline in MMSE scores over the same time period among people with dementia [26, 27]. Furthermore, a similar study by Richeson et al. [28] found evidence that health promotion leads to improved self-efficacy in people with early-stage dementia. Other studies of health promotion for people with early-stage dementia have reported improved nutrition, health related quality of life, prevention of falls [29], and improvement in physical function [30]. A systematic review by Boots et al. [31] found beneficial effects of internet-based interventions for care partners of people with dementia. The review demonstrated improvement in various aspects of carer wellbeing, e.g. confidence, depression and self-efficacy, given that the programs include multiple components and are tailored to the individual.

### Study objectives

The primary objective is to determine whether the integrated 10-week SHAPE intervention, combining self-management and health promotion for people with dementia and e-learning for care partners, will significantly improve self–efficacy in people with mild to moderate dementia. Secondary objectives are to determine the impact of the SHAPE intervention on mood, well-being, quality of life, health behaviours, cognition, neuropsychiatric symptoms, carer stress, knowledge of dementia, and to assess cost-effectiveness in people with dementia and their care partners. Furthermore, we wish to qualitatively explore and describe barriers and promoting factors for uptake and implementation, and capture motivational and empowering elements of the intervention and to explore the intervention’s impact on self-efficacy and wellbeing.

### Hypotheses

We hypothesise that the intervention will significantly improve self-efficacy in people with dementia compared to treatment as usual. Secondary hypotheses are that the integrated SHAPE intervention will improve wellbeing and other key health and mental health outcomes for people with dementia (e.g. depression, anxiety, health-promoting behaviour, and quality of life), reduce stress and increase knowledge of dementia for care partners, and provide a cost-effective approach to improving outcomes for people with dementia and their families.

### Assessment and management of risk

This is a low-risk, non-pharmacological trial [32]; in such trials, certain adverse events are not required to be reported, but should be recorded. Minimal risk of psychological stress may occur as a result of assessments (e.g. completing a depression scale). Should psychological distress occur, the research team will provide participants with information about local resources that will assist with their distress.

If a participant is hospitalised during the intervention, this will be recorded. No deaths are anticipated as a result of the intervention. However, if a participant dies during the trial period, follow-up assessments that include the care partner will be discontinued.

## Methods/design

This protocol is reported with reference to the SPIRIT checklist [33] (Additional file 1).

### Overall design

This is a multi-site, controlled, single block-randomised, single-blinded trial with parallel arms. The intervention arm is compared with treatment as usual (TAU).

### The SHAPE intervention

The SHAPE intervention is based on the Corbin and Strauss Trajectory Model [34], and combines approaches of self-management, health promotion, and e-learning. The intervention is designed to develop self-management skills in areas including decision-making, symptom management and social interaction and to provide information on the disease process and the development of healthy behaviours in a supportive learning environment. The intervention comprises ten weekly 2-h group sessions for persons with dementia, where each session is led by two trained facilitators at each study site. The group facilitators will have professional clinical training e.g. nursing, occupational therapy, and psychology and have experience of working with people with dementia. For the care partners involved as study partners, the same material presented in the 10-week SHAPE course for people with dementia, plus some additional material and signposting to support them in their role, will be delivered through an online e-learning platform. Key themes of the intervention will include positive actions to improve and maintain health, how to talk about the impact of the disease on the life of the person with dementia, addressing the fear of losing independence and how to tackle and solve other sensitive issues (Table 1).

**Table 1 Tab1:** Key themes covered in the intervention

Sessions	Topic
Session 1	Orientation to the course
Session 2	Healthy lifestyle, doctor’s visits and use of medication
Session 3	Healthy eating, diet and nutrition
Session 4	Staying safe
Session 5	Exercising body and brain
Session 6	Activities, interests and learning
Session 7	Managing memory difficulties
Session 8	Adapting and coping
Session 9	Relationships and communication
Session 10	Planning for the future

### Control arm

Participants randomised to TAU will continue to receive usual care and support, which may include a regular nurse-led clinical review and access to services such as psychiatry, occupational therapy and social services as needed. Using TAU as a comparator condition ensures that all participants receive needed services and allows for a comparison between the new intervention and current best practice. However, after the intervention is completed, the TAU group will be offered the intervention. Furthermore, all participants in the TAU group will be given the link to the e-learning comprising the complete educational programme of the intervention once the trial has ended. Schedule of enrolment, intervention, and assessments for the SHAPE trial are presented in Fig. 1.

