### Outcome and study eligibility measures

All quantitative outcome measures will be assessed prior to randomisation (baseline), after the intervention (follow-up 1) and then 6 months after follow-up 1 (follow-up 2). The assessments will consist of questionnaires using standardised, evidence-based scales and other information obtained from the participant and appointed care partner. The interviews will be conducted with the participant and care partner, both together and separately. Participant and care partner demographic details will be collected.

The primary outcome in the SHAPE trial is self-efficacy measured by the General Self-Efficacy Scale (GSES) [39]. The secondary outcome measures include cognition assessed with the Mini Mental State Examination (MMSE) [40], which is also used to check eligibility, depressive symptoms measured by the Cornell Scale for Depression in Dementia (CSDD) [41], quality of life and well-being measured by the Dementia Quality of Life Scale (DEMQOL) [42], health-related quality of life measured by EQ-5D-5L [43], neuropsychiatric symptoms measured by the Neuropsychiatric Inventory Questionnaire (NPI-Q) [44], health behaviour changes measured by the SHAPE research team health reporting form, use of support services measured by the Client Services Receipt Inventory (CSRI) [45], carer stress measured by the Relative‘s Stress Scale (RSS) [48], carer sense of competence measured by the Short Sense of Competence Questionnaire (SSCQ) Short version [49], and knowledge about dementia measured by the Dementia Knowledge Assessment Scale (DKAS) [50]. We will use the Clinical Dementia Rating Scale (CDR) [39] to measure level of dementia and to measure functional changes in the participants we will use the Functional Activities Questionnaire (FAQ) [40]. A full description of the primary and secondary outcomes and screening instruments is provided in Table 2.

**Table 2 Tab2:** Description of measures

Measures	What does the tool measure	Informant	Tool characteristics and psychometric properties
CDR [49]	Diagnostic criteria	Care partner	Assesses six domains of cognitive and functional performance: memory, orientation, judgment & problem solving, community affairs, home & hobbies, and personal care. 0 = no cognitive impairment, 0.5 = questionable or very mild dementia, 1, 2 and 3 for mild, moderate and severe dementia. Scores in each of these are combined to obtain a composite score ranging from 0 (none) through 3 (severe).

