### Statistical analysis

All outcome measures will be reported at baseline, after the intervention (follow up 1) and at 6-months after follow-up 1 (follow up 2). Baseline characteristics (age, gender, ethnicity, civil status, education, living situation, use of medication) will be presented for each intervention group and by site. Trial analysis will include all participants with allocation to study arms as randomised, i.e. on an intention-to-treat basis.

The primary outcome measure (GSES) [39] will be analysed using the multilevel modelling approach to analysis of covariance (ANCOVA), i.e. with follow-up GSES as dependent variable and with study arm, site Norway 1, Norway 2, UK and Australia, baseline GSES, time since baseline assessment, other baseline variables predictive of the outcome, as well as potential variables constituting baseline imbalance between study arms, as independent variables, while allowing for clustering within treatment groups [57]. The estimate of the effect of the intervention will be reported with a 95% confidence interval and associated *p*-value. Missing outcome data will be handled by including any variables predictive of missingness in a complete case-analysis of the multilevel ANCOVA model [58]. The estimate of the effect of the intervention will be reported with a 95% confidence interval and associated *p*-value. Secondary outcomes will be analysed similarly.

Multiple imputation (MICE) will be used for sensitivity analysis to assess the robustness of the results to differential loss to follow up [58].

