## Discussion

The integrated SHAPE intervention represents a novel and different approach combining self-management and health promotion for people with dementia and e-learning for care partners. It is based on health promotion and self-management and on the imperative to maintain the dignity and autonomy of the person with dementia and support him or her in planning for the future together with the family. The adjunctive e-learning platform will provide care partners with the same information that the person with dementia receives plus some additional material and signposting to support them in their role. This will further empower the whole family to support and enable more effective self-management by the person with dementia, and enhance their ability to plan ahead together and make key decisions jointly - such as how and when to communicate their needs to health care services and to receive appropriate care at the right time. Being able to talk openly about the disease process and future challenges with family members in the early stage of the disease can be empowering for everyone involved. The website with the e-learning resources provided to the care partners will collect information on website use. The e-learning component will also be created in a version which does not collect any data on the user. The purpose of this is so it can be distributed to other people in the support network of the person with dementia, and it therefore has the potential to reach those who live in regional, rural and remote areas.

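### The offer of the course to the TAU arm is not tied to follow-up 2 and, read literally, precedes it, so comparisons that use follow-up 2 would be diluted in proportion to uptake

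*Protocol article*

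**What the plan says.** The Control arm section contains two consecutive statements about what TAU participants will later receive:

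- The course: "However, after the intervention is completed, the TAU group will be offered the intervention".
- The e-learning link, which comprises the "complete educational programme of the intervention once the trial has ended".

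The section on outcome and study eligibility measures places the post-baseline assessments "after the intervention (follow-up 1) and then 6 months after follow-up 1 (follow-up 2"). On course length, the section on the SHAPE intervention states: "The intervention comprises ten weekly 2-h group sessions for persons with dementia".

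The comparison is described throughout as SHAPE against usual care. Overall design says "The intervention arm is compared with treatment as usual (TAU"), and Statistical analysis says "Trial analysis will include all participants with allocation to study arms as randomised, i.e. on an intention-to-treat basis". That section names the primary dependent variable only as the follow-up GSES score. The Economic evaluation section divides the SHAPE-minus-TAU difference in costs by the difference in outcomes, and the article gives no time horizon for it. Neither section mentions TAU participants who have taken the course.

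**The concern.** The two sentences in Control arm use different release points for the same arm. The second shows that the authors could write end of trial when they meant it. The first uses completion of the intervention, which is also how the article places FU1. On that reading the offer opens at about FU1, and a ten-week course fits comfortably inside the 6 months before FU2.

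A TAU participant who takes up the offer is then no longer receiving usual care alone when assessed at FU2, yet is analysed as TAU. Three results are at stake: the FU2 contrast for every outcome, the primary GSES result if it uses or pools FU2, and any cost or QALY difference accumulated to FU2. The bias is towards no difference. It cannot be undone once TAU participants have attended.

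**Working it through.** **1. Timing under the literal reading.** Ten weekly sessions take about 2.3 months, and the gap from FU1 to FU2 is 6 months. A TAU participant offered the course at FU1 can finish it with more than 3 months to spare before FU2.

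**2. Timing under a lenient reading.** Suppose completion means that every course in the whole trial has finished. Planned recruitment rate has course groups starting from month 3 to month 15, with at least one new group per centre every 1.5 months. On that grid there are nine waves: months 3, 4.5, 6, 7.5, 9, 10.5, 12, 13.5 and 15.

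- Last course ends: 15 + 2.3 = month 17.3.
- FU2 for a wave: start + 2.3 + 6 = start + 8.3 months.
- FU2 falls after month 17.3 for starts later than month 9. These are the waves at 10.5, 12, 13.5 and 15, or 4 of 9.
- A TAU participant starting at month 17.3 finishes at 17.3 + 2.3 = month 19.6. The waves at 12, 13.5 and 15 have FU2 at months 20.3, 21.8 and 23.3, so 3 of 9 could finish the whole course before FU2.

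The lenient reading protects the early waves but not the late ones.

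**3. The plan's sample size.** Inputs from the Sample size section: SMD 0.4, 90% power, 5% significance (two-sided assumed), R² = 0.25, ICC 0.1, groups of 8, 6 analysed per group, 2:1 allocation, 25% attrition.

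- Unadjusted: 2 × (1.960 + 1.282)² / 0.16 = 131.3, so 132 per arm (264). The t-test version needs 132.3, so 133 per arm (266). The stated 268 is within 2% of both.
- Covariate adjustment: 268 × 0.75 = 201, as stated.
- With the design effect in the intervention arm only, TAU recruits = (132.3 / 2) × 0.75 × (1 + DE/2) / 0.75. With DE = 1 + 7 × 0.1 = 1.7 this is 122.4, so 123 TAU and 246 intervention, as stated.

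No planned figure is in dispute.

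**4. Power at FU2 as a function of TAU uptake.** The protocol states no standard error, so one is built from its inputs. Recruiting 248 and 124 with 25% attrition leaves 186 and 93 analysed. With 6 per group, DE = 1 + 5 × 0.1 = 1.5.

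SE = √(0.75 × 1.5 / 186 + 0.75 / 93) = √0.01411 = 0.119 SD.

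If a share u of TAU takes the course before FU2 and gains its full effect, the intention-to-treat SMD is 0.4 × (1 − u), and power is Φ(SMD / SE − 1.96).

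| Assumed uptake u | SMD at FU2 | Power |
|---|---|---|
| 0% | 0.40 | 92% |
| 10% | 0.36 | 86% |
| 25% | 0.30 | 71% |
| 50% | 0.20 | 39% |
| 75% | 0.10 | 13% |

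If takers gain only a fraction f of the effect, u is replaced by u × f. For example, 50% uptake with half the benefit gives 0.5 × 0.5 = 0.25, which is the 25% row. Clustering among TAU participants who attend groups is ignored, so the figures are slightly optimistic on that count.

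**The case against.** The strongest reply is that nothing in the article says the offer comes before FU2. The word intervention elsewhere includes the e-learning. Since TAU gets that link only at the end of the trial, the full package could not be offered sooner, and the first sentence may mean the same date. Completion may also refer to the trial as a whole. Fig. 1, the schedule, could not be read for this review and might settle the matter. A delayed offer to controls is also a recognised design choice.

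Part of this stands. The pre-FU2 timing is an inference from the wording, not an explicit statement. But no text ties the offer to FU2, and the trial-wide reading still leaves late waves exposed. Even if Fig. 1 is clear, the two sentences need to agree with it.

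Some stronger conclusions are tempting but not supported:

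- **That FU2 loses its control group.** The offer is voluntary and uptake is unknown. The randomised contrast survives as immediate versus delayed offer.
- **That TAU costs would contain course delivery.** The Economic evaluation section collects intervention costs on separate study forms and does not say how a course delivered to TAU would be costed.
- **That the untracked e-learning version is a further leak.** The Discussion says "The e-learning component will also be created in a version which does not collect any data on the user", but describes it as meant for others in the person's support network. Nothing gives it to TAU during follow-up.
- **That a power figure can be put on an average of FU1 and FU2.** This needs the correlation between visits, which the article does not give, and no section says that the visits are averaged.

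**Conclusion.** The concern holds as a badly fixed rule. As worded, the protocol permits TAU participants to take the course before FU2, and its analysis and economic sections make no provision for that. If they do, the FU2 intention-to-treat contrast, any primary GSES analysis that uses FU2, and any cost or QALY comparison running to FU2 shrink towards zero in proportion to uptake. Under the assumptions shown, 10% uptake already takes FU2 power below the planned 90%, and 50% takes it below 40%.

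The size rests on three assumptions: an uptake that the article does not give, full benefit in takers, and a true effect of 0.4 SD that persists to FU2. The Sample size section claims power for the primary analysis, not for FU2 specifically. FU1 is unaffected provided the offer follows the FU1 assessment, and an economic analysis that stops at FU1 would keep its comparator.

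**What to change.** Reconcile the two sentences in Control arm with each other and with the outcome, Economic evaluation and Statistical analysis sections, by stating whether the course is offered before or after each participant's FU2. The e-learning link is tied to the end of the trial, not to individual FU2 dates, so its wording should be checked at the same time.

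- **If the offer follows FU2:** the SHAPE-versus-TAU comparison is kept at both follow-ups. The cost is a wait about 6 months longer for TAU participants, with a possible effect on retention in that arm. No extra participants or visits are needed.
- **If the offer precedes FU2:** place it after the FU1 assessment, record which TAU participants attend and when, limit SHAPE-versus-TAU conclusions to FU1, and label FU2 and longer-horizon economic results as immediate versus delayed offer. The cost is attendance recording in TAU and a narrower claim at FU2.

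Either way it is a change of a few sentences, with matching text in the participant information. Trial status says that recruitment had not opened when the article was submitted, so the change could be made before anyone was randomised.
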